## Abstract

**Background:**

As an irreversible, intractable disease with vision loss, glaucoma leads to permanent and progressive damage of visual function. Lowering high intraocular pressure (HIOP) is the first choice for treating glaucoma; however, the control of HIOP is not enough to prevent progressive vison loss. Currently, the therapies to treat glaucoma with controlled IOP (GPCI) are unsatisfactory. Chinese medicine is effective for improving visual function in patients with GPCI. Bujing Yishi tablets (BJYSP) have been the standard preparation for treating GPCI in our hospital for decades. However, no rigorous randomized controlled clinical studies have investigated its effects and safety.

**Methods:**

This study will be a 6-month, multicenter, stratified trial following a prospective, randomized, open-label, blinded endpoint (PROBE) protocol. A total of 216 eligible GPCI patients aged 18–75 years will be stratified according to the early, moderate, and advanced stages of glaucoma. After stratifying, the participants will be randomly assigned to the BJYSP group or control group at a ratio of 1:1. Following randomization, participants in the BJYSP group and control group will receive BJYSP and mecobalamin tablets, respectively, for the same 6-month period. The primary outcomes will include the best-corrected visual acuity (BCVA), visual field assessment, visual evoked potential (VEP) test, and Heidelberg retina tomography II (HRT II); the secondary outcomes will include intraocular pressure (IOP) and Traditional Chinese medicine (TCM) clinical symptom scales. The primary and secondary outcomes will be measured at baseline and 8, 16, and 24 weeks thereafter. Safety assessments will also be evaluated at baseline and 12 and 24 weeks thereafter.

**Discussion:**

This study will be a standardized, scientific, clinical trial designed to evaluate the therapeutic effects and safety of BJYSP as a novel therapeutic strategy for improving visual function in patients with GPCI.

**Trial registration:**

Chinese Clinical Trial Registry, ChiCTR1800016431. Registered on 1 June 2018.

## Administrative information

Note: the numbers in curly brackets in this protocol refer to SPIRIT checklist item numbers. The order of the items has been modified to group similar items (see http://www.equator-network.org/reporting-guidelines/spirit-2013-statement-defining-standard-protocol-items-for-clinical-trials/).

## Introduction

### Background and rationale {6a}

Glaucoma, affecting approximately 80 million people, is a leading cause of irreversible blindness worldwide. Degeneration of retinal ganglion cells (RGC) and progressive loss of the visual field are the primary features of glaucoma [1]. Reducing intraocular pressure (IOP) is presently the most practiced therapeutic approach for glaucoma. However, progressive loss of vision or blindness can still occur in some patients with glaucoma with controlled IOP (GPCI) [2]. It is now recognized that neuroprotective therapies are crucial in the management of glaucoma [3]. The main research on optic neuroprotective treatments have included antioxidants, N-methyl-D-aspartate (NMDA) receptor antagonists, inhibitors of glutamate release, calcium channel blockers, polyamine antagonists, nitric synthase inhibitors, and vitamin B1 [4]. Nevertheless, to date, there is no satisfying neuroprotective agent for patients with glaucoma. Gene therapy and stem cell-based applications are promising, yet they are still undergoing clinical trials. To this end, finding a satisfactory effective therapy might be a favorable way to prevent the development of glaucoma.

Traditional Chinese medicine (TCM) therapy has been used to treat glaucoma for thousands of years and has demonstrated a more favorable safety profile than conventional medicine [5, 6]. In TCM, the same disease could be diagnosed as comprising various syndromes. Therefore, the same disease will be treated differently according to the different syndromes. The syndrome of “*liver-kidney deficiency, blood stasis and fluid retention*” is an important subtype in GPCI [7, 8]. The *Bujing Yishi* tablet (BJYSP) (Good Manufacturing Practice Certificate No: 20160003HZ) is the optic nerve protector that was inherited from the legacy of [name], who is a renowned TCM ophthalmologist in China. BJYSP consists of 10 herbs, including *salvia miltiorrhiza*, *notoginseng*, *fructus broussonetiae*, *semen cuscutae*, *schisandra chinensis*, *Chaenomeles sinensis*, motherwort fruit, *medlar*, *semen plantaginis*, and *citri reticulatae pericarpium viride*. According to TCM theory, these herbs make a concerted effect to nourish the liver and kidneys, promote blood circulation, and dredge collaterals. The therapeutic effect of BJYSP is precisely for the syndrome of “*liver-kidney deficiency, blood stasis and fluid retention*.” The safety and quality control of BJYSP is supervised by Sichuan Food and Drug Administration according to its criterion of SZBZ20070647–10(Z). We have proven many times that BJYSP protects the optic nerve from glaucoma in a glaucoma rat model; that is, BJYSP results in upregulating retinal phosphorylation-protein kinase B (P-AKT) of phosphoinositide-3 kinase (PI3K)/protein kinase B (AKT) signaling and slightly decreasing IOP [9], promoting the secretion of brain-derived neurotrophic growth factor (BDNF) and Nissl bodies [10, 11], increasing the numbers of RCGs, and improving the thickness of the retina nerve fiber layer (RNFL) and retinal ganglion cell layer (RGCL) and the ultrastructure of RCGs in a rat model of glaucoma [12].

### Objectives {7}

Although BJYSP was approved by the Sichuan Food and Drug Administration for the clinical use for hypofunction of the optic nerve and retina in 2007, it has a good effect in the treatment of patients with GPCI in the clinical setting. However, there is not enough rigorous scientific evidence to show that BJYSP is effective in treating patients with GPCI. Hence, the aim of the present study was to clarify the visual function protective effects of BJYSP by comparing it with a positive control drug (mecobalamin tablet) in patients with GPCI.

### Trial design {8}

The study is designed as a 6-month, multicenter, stratified trial following the prospective, randomized, open-label, blinded endpoint (PROBE) study. The purpose is to evaluate the safety and effect of BJYSP in patients with GPCI. The clinical study was approved by the Sichuan Regional Ethics Review Committee on Chinese Medicine and Medical Ethics Committee of Affiliated Hospital of Chengdu University of TCM (approval no. 2018KL-040). The study was registered at the Chinese Clinical Trial Registry (ChiCTR1800016431, website: http://www.chictr.org.cn). The study will be strictly conducted according to the principles of the Declaration of Helsinki as well as Good Clinical Practice (GCP) guidelines. The trial will be completed according to the Standard Protocols Items: Recommendations for Intervention Trials (SPIRIT) Checklist.

## Methods: participants, interventions, and outcomes

### Study setting {9}

Potential participants with GPCI will be recruited from the Hospital of Chengdu University of TCM (Sichuan, China), MianYang Hospital of TCM (Sichuan, China), and The Second People’s Hospital of Chengdu PiDu District (Sichuan, China). Our research will use the Internet, hospital announcements, and posters to provide a hotline to call for potential volunteers. If the patients are interested in our study, they will be told of the purpose and content of research as well as the benefits and drawbacks of participating in detail. After screening, the participants meeting the inclusion criteria will be enrolled. The study flow is shown in in the SPIRIT Figure (Fig. 1). Participants will undergo a 6-month treatment period and a 6-month follow-up period.

**Fig. 1 Fig1:**
[figure not shown]
Flow chart of clinical trial in patients with GPCI. BJYSP Bujing Yishi tablet, GPCI glaucoma with controlled IOP, IOP intraocular pressure

### Eligibility criteria {10}

#### Inclusion criteria

All eligible participants should meet the following criteria: (1) diagnosed with primary open-angle glaucoma (POAG) [13]: pathologic high intraocular pressure (HIOP; 24 h peak IOP > 21 mmHg (1 mmHg = 0.133 kPa), characteristic glaucomatous neuropathy (RNFL defect or optic disc change), and/or visual field loss, open anterior chamber angle, exclusion of other causes result in HIOP, only one eye from each patient will be chosen; (2) have a visual field defect that could be evaluated by standard automated perimetry (reliability factor < 15%) and an IOP that is < 18 mmHg (at least 3 months after anti-glaucoma surgery); (3) meet the syndrome pattern of kidney deficiency and blood stasis; (4) withdraw from using other optic nerve protective agents for > 2 months; (5) have spherical refractive error between + 3.00 and − 6.00 diopters, clearly visible fundus without pupil dilation, and best-corrected visual acuity (BCVA) ≥ 0.3; (6) be aged 18–75 years; (7) be in a conscious status and able to cooperate with the examination and treatment; and (8) be willing to take part in the study and sign informed consent.

#### Exclusion criteria

Participants with any one of the following will be excluded: (1) poorly controlled IOP (≤ 7 mmHg or > 18 mmHg) accompanied by thin filtering cystic bleb or bleb leakage; (2) glaucoma other than open-angle glaucoma; (3) a syndrome pattern that does not meet the criteria of kidney deficiency and blood stasis; (4) other macular degeneration, cataract, proliferative diabetic retinopathy, and retinal vascular occlusion or other diseases that might cause visual field loss; (5) pregnancy or lactation; (6) abnormal severe primary hepatic or renal or serious systemic diseases such as heart diseases, primary hypertension, diabetes mellitus, or gastric ulcer; or (7) an allergic history to the ingredients of BJYSP or mecobalamin tablets.

#### TCM syndrome differentiation

The TCM syndrome of kidney deficiency and blood stasis will be based on guidelines delineated in the *Clinical Research of New Investigational Drugs in Traditional Chinese Medicine* [14]. The diagnostic standards are as follows: primary signs and symptoms include blurry visual acuity, narrow visual field, and eye distension; and secondary signs and symptoms include dry eye, limp aching lumbus and knees.

For the diagnosis of GPCI, participants will be diagnosed with both kidney deficiency and blood stasis syndrome under the condition of meeting at least two of the primary signs/symptoms and two or more secondary signs/symptoms, and the necessary condition is dark purple tongue and thready pulse with deep, or string, or unsmooth. The investigators will be required to be trained in standard operating procedures (SOPs) of scrutinization of TCM symptoms and administer a symptom assessment survey to every participant according to TCM Symptom Score Scale (Table 1).

**Table 1 Tab1:** Traditional Chinese medicine (TCM) symptom score scale

Blurry visual acuity	▫ 0: None
	▫ 2: Mild blurred visual acuity
	▫ 4: Unable to read
	▫ 6: Difficult to see anything
Narrow visual field	▫ 0: None
	▫ 2: As if something obscures visual acuity
	▫ 4: Inconvenient to walk
	▫ 6: Difficult to walk
Eye distension	▫ 0: None
	▫ 2: Mild eye distension
	▫ 4: Endurable eye distension
	▫ 6: Intolerable eye distension
Dry eye	▫ 0: None
	▫ 2: Mild dry eye
	▫ 4: Obvious dry eye, as if there is a foreign body in it
	▫ 6: Intolerable dry eye, frequent blink
Limp aching lumbus and knees	▫ 0: None
	▫ 2: Early morning aching lumbus, which can be alleviated by beating; mild limp knees
	▫ 4: Continuous aching lumbus, which will be aggravated when working knees are too limp to carry heavy weight
	▫ 6: Severe aching lumbus, which will not be relieved by rest; knees are too limp to desire to walk
Dark purple tongue	▫ 0: No
	▫ 2: Yes
Thready pulse deep, string or unsmooth	▫ 0: No
	▫ 2: Yes

### Who will take informed consent? {26a}

[name], [name], and [name] will obtain informed consent from potential trial participants at each site, respectively.

### Additional consent provisions for collection and use of participant data and biological specimens {26b}

Not applicable.

### Interventions

#### Explanation for the choice of comparators {6b}

In this trial, we will investigate whether BJYSP can effectively protect the optic nerve and improve visual function for GPCI. The mecobalamin tablets are currently being used as a routine treatment for treating visual function impairment of GPCI [15, 16]. Therefore, mecobalamin was chosen as a positive-control medicine in our trial. In addition, to observe the effect of BJYSP on GPCI with different disease severity, GPCI will be classified as early, moderate, and advanced based on the visual field defects of patients.

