### Assignment of interventions: allocation

#### Sequence generation {16a}

After obtaining the written informed consent from the participants and baseline screening, all eligible patients will be stratified according to early, moderate, and advanced stages of glaucoma [20]: early glaucoma patients have an early glaucomatous visual field loss defined as an MD ≥ − 6 dB; moderate glaucoma patients have a moderate glaucomatous visual field loss defined as MD ≤ − 6 to ≥ − 12 dB; and advanced glaucoma patients had an advanced glaucomatous visual field loss defined as MD ≤ − 12 to ≥ − 20 dB. Random numbers of 001–216 will be automatically generated by SAS software (whole random numbers). Among them, the random numbers 001–072 are assigned to the early stage, the random numbers 073–144 are assigned to the moderate stage, and the random numbers 145–216 are assigned to the advanced stage. After stratifying, the participants will be randomly assigned to the BJYSP group or control group with a ratio of 1:1. An overview of case distribution of each center, specific measurements, and time points of data collection can be found in the SPIRIT Figure (Fig. 2).

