### Statistical methods

#### Statistical methods for primary and secondary outcomes {20a}

Statisticians will independently undertake statistical analysis. All data will be presented as the means ± standard deviation (SD). Statistical analysis will be performed by SPSS 21.0 software (SPSS Inc., Chicago, IL, USA). All statistical tests will be two-sided tests, and the statistical significance threshold will be set at *P* < 0.05. The chi-square test will be used for categorical variables, an independent Student’s t-test will be used on measurement data, and rank-sum test will be used for grade data. To assess covariate balance, baseline characteristics will be summarized and compared between the BJYSP group and the control group by means of simple descriptive statistics.

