#### Methods for additional analyses (e.g. subgroup analyses) {20b}

Not applicable.

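### Patients are staged in order to see the effect by disease severity, yet subgroup analysis is marked as not applicable, and the stage definitions overlap and stop at −20 dB

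*Protocol article*

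**What the plan says.** The Protocol article gives its reason for staging patients as early, moderate or advanced under Explanation for the choice of comparators {6b}: "to observe the effect of BJYSP on GPCI with different disease severity". The Discussion repeats the sentence.

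Sequence generation {16a} builds the stages into the randomisation: "all eligible patients will be stratified according to early, moderate, and advanced stages of glaucoma". In the numbering, "the random numbers 001–072 are assigned to the early stage, the random numbers 073–144 are assigned to the moderate stage", and 145–216 go to the advanced stage. After that, "the participants will be randomly assigned to the BJYSP group or control group with a ratio of 1:1".

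The same section defines the stages by visual field MD. The first definition begins "early glaucoma patients have an early glaucomatous visual field loss defined as an MD" and sets the limit at −6 dB or better. Moderate runs from −6 to −12 dB and advanced from −12 to −20 dB, with both ends included each time.

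Statistical methods {20a} states: "The chi-square test will be used for categorical variables, an independent Student’s t-test will be used on measurement data", with a rank-sum test for graded data. The next relevant item, Methods for additional analyses {20b}, names subgroup analyses in its heading, and its whole content is that the item is not applicable.

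**The concern.** A purpose is stated, the design is shaped around it, and the analysis it needs is then ruled out. A team that follows the article will report BJYSP against mecobalamin overall and nothing by stage, so the question that the article gives as its reason for staging stays open. A team that wants the by-stage answer will have to depart from {20b}, with no rule fixed in advance on which outcomes to use, how to compare stages, or what may be claimed.

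The stage definitions matter for the same reason. They decide which block of random numbers a patient draws from and which group that patient would belong to in any by-stage analysis. Where a patient fits two stages or none, the article does not say what happens.

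**Working it through.** **1. The sections side by side.**
- {6b} and Discussion: staging serves to see the effect at different severities.
- {16a}: three strata of 72 numbers; 3 × 72 = 216, the full sample; 72 / 2 = 36 per arm.
- {20a}: two-group tests, with no analysis by stage.
- {20b}: subgroup analyses do not apply.

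No other section describes an analysis by severity. The first two entries call for one, and the last excludes it.

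**2. The stage limits in {16a}.**
- MD = −6 dB satisfies early (≥ −6) and moderate (≤ −6).
- MD = −12 dB satisfies moderate (≥ −12) and advanced (≤ −12).
- MD < −20 dB satisfies none. Eligibility criteria {10} require a field defect that perimetry can evaluate with a reliability factor below 15%, but set no MD limit. Such a patient can be eligible and have no stratum and no random number.

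**3. What the sample size was built for.** Sample size {14} uses n = ½[(1.96 + 1.282) / (asin√0.67 − asin√0.871)]². The arcsine difference is 0.2446 in absolute value, so n = ½(3.242 / 0.2446)² ≈ 87.86, as printed; 88 per arm. This is for the overall comparison, with about 90% power.

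The same formula turned round gives power = Φ(√(2n) × 0.2446 − 1.96):
- 36 per arm in one stage: Φ(2.075 − 1.96) ≈ 55%.
- 29 per arm (36 × 0.8 = 28.8, using the 20% dropout in {14}): Φ(1.863 − 1.96) ≈ 46%.
- Contrast of two stages, assuming the full effect in one and none in the other, 36 per arm: Φ(0.2446 / √(2/72) − 1.96) ≈ 31%.

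These use the rates put into the formula. The text of {14} speaks of 85% and 90% instead; with those, power within a stage of 36 per arm would be about 9%. That mismatch is a separate matter and does not change this point.

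**4. Precision by stage.** The primary outcomes in {12} are mean changes, so SD units are natural. Assuming a common SD, the 95% CI half-width for a difference between arms is 1.96 × √(2/n) SD:
- Overall, n = 108: 0.27 SD.
- One stage, n = 36: 0.46 SD.
- One stage after 20% loss, n = 29: 0.51 SD.
- Difference in effect between two stages, 1.96 × √(4/36): 0.65 SD.

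**The case against.** The best defence is that stratified randomisation is worth having for balance alone and that Objectives {7} contains no aim by severity. The sentence in {6b} is a rationale, its verb is a modest one, and the trial is sized only for the overall comparison. This stands as a limit on the importance of the point: the purpose is subsidiary and the main comparison does not depend on it. It does not remove the contradiction, because balance is not the reason that the article gives.

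A second defence is that a statistical analysis plan, not shown, may hold the by-stage analysis. Had {20b} been silent, that would be a full answer, and the lack of a stage term in {20a} alone would be no finding. But {20b} addresses subgroup analyses and rules them out, so a plan that added them would contradict the protocol.

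Two stronger readings are tempting, and the article supports neither.
- A reader might infer that staff who know the treatment could steer patients on a boundary into a chosen stratum. In {16a} staging comes before assignment, and Concealment mechanism {16b} keeps the numbers in sealed envelopes and the sequence from the investigators. The definitions leave the stratum undetermined, but that does not show that it could be chosen with knowledge of treatment.
- A reader might infer a false-positive risk of about 14% (1 − 0.95³ = 0.143) from testing each stage at 0.05. The plan contains no such tests. The figure describes a hypothetical departure from it, with independent tests of one outcome and no true effect.

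It is also fair to say that the overlap touches only exact values of −6 and −12 dB. The article does not say how many patients to expect there or below −20 dB.

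**Conclusion.** The point holds, at moderate weight. The article states a purpose, builds three strata of 72 around it, and then excludes the analysis that would serve it. As printed, the stage definitions also cannot be applied to an MD of exactly −6 or −12 dB, or to one below −20 dB. The validity and size of the overall comparison are not in question.

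The imprecision figures describe what a by-stage analysis could deliver; they do not measure harm done by the inconsistency. They assume that every stage fills to 72, that allocation within a stage comes out at 36 per arm and, for the half-widths, a continuous outcome with a common SD. On those assumptions a stage-specific interval is about 1.7 times as wide as the overall one (0.462 / 0.267), which is enough for description but not for a claim of benefit confined to one stage.

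**What to change.** 1. In {20b}, replace the present entry with an exploratory analysis by the stage used at randomisation. For a short, named list of main outcomes at month 6, report the treatment difference and 95% CI in each stage, and test treatment-by-stage interaction in a linear model with treatment, stage and their interaction. Three stages give two interaction terms, hence a test on two degrees of freedom. State that no efficacy claim for a single stage will rest on a within-stage p-value. The outcomes must be named because {12} lists 21 primary measures (1 acuity, 3 field, 4 VEP, 13 HRT II) and {20a} has no model to which a term could simply be added.
2. If the sponsor does not want this analysis, withdraw the purpose stated in {6b} and the Discussion instead.
3. In {16a}, assign each boundary value to one stage only, and reconcile the −20 dB limit with {10} so that every eligible patient has a stratum. How to do so is for the sponsor to decide. Since recruitment began in June 2018, also record how any such patients already enrolled were staged.

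The cost is protocol wording and one additional model for each named outcome. The allocation ratio and sample size need not change. The price is the wide intervals by stage, which the report should state openly.

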#### Intervention description {11a}

Participants will receive BJYSP or mecobalamin tablets for 6 months. The BJYSP (0.3 g/ tablet × 5) and mecobalamin tablets (0.5 mg/ tablet × 1) will be orally administered three times a day for 6 months in the BJYSP group and control group, respectively. BJYSP is provided by the Teaching Hospital of Chengdu University of TCM, Chengdu, China (Good Manufacturing Practice Certificate No: 20160003HZ). BJYSP consists of 10 herbs, including *salvia miltiorrhiza*, *notoginseng*, *fructus broussonetiae*, *semen cuscutae*, *schisandra chinensis*, Chaenomeles sinensis, motherwort fruit, *medlar*, *semen plantaginis*, and *citri reticulatae pericarpium viride*. According to TCM theory, these herbs make a concerted effect to nourish the liver and kidneys, promote blood circulation, and dredge collaterals. The safety and quality control of BJYSP is supervised by Sichuan Food and Drug Administration according to its criterion of SZBZ20070647–10 (Z). Mecobalamin tablets are provided by North China Pharmaceutical Co. Ltd., Shijiazhuang, China (Approval no. H20031126). Participants will be advised to refrain from other treatments during the study. The study will also include IOP-control medicine without the effect of optic nerve protection such as β-adrenergic blockers, adrenergic agonists, and carbonic anhydrase inhibitors.

